## Abstract

**Background:**

As part of the German Medical Informatics Initiative, the MIRACUM project establishes data integration centers across ten German university hospitals. The embedded MIRACUM Use Case “Alerting in Care - IT Support for Patient Recruitment”, aims to support the recruitment into clinical trials by automatically querying the repositories for patients satisfying eligibility criteria and presenting them as screening candidates. The objective of this study is to investigate whether the developed recruitment tool has a positive effect on study recruitment within a multi-center environment by increasing the number of participants. Its secondary objective is the measurement of organizational burden and user satisfaction of the provided IT solution.

**Methods:**

The study uses an Interrupted Time Series Design with a duration of 15 months. All trials start in the control phase of randomized length with regular recruitment and change to the intervention phase with additional IT support. The intervention consists of the application of a recruitment-support system which uses patient data collected in general care for screening according to specific criteria. The inclusion and exclusion criteria of all selected trials are translated into a machine-readable format using the OHDSI ATLAS tool. All patient data from the data integration centers is regularly checked against these criteria. The primary outcome is the number of participants recruited per trial and week standardized by the targeted number of participants per week and the expected recruitment duration of the specific trial. Secondary outcomes are usability, usefulness, and efficacy of the recruitment support. Sample size calculation based on simple parallel group assumption can demonstrate an effect size of *d*=0.57 on a significance level of 5% and a power of 80% with a total number of 100 trials (10 per site). Data describing the included trials and the recruitment process is collected at each site. The primary analysis will be conducted using linear mixed models with the actual recruitment number per week and trial standardized by the expected recruitment number per week and trial as the dependent variable.

**Discussion:**

The application of an IT-supported recruitment solution developed in the MIRACUM consortium leads to an increased number of recruited participants in studies at German university hospitals. It supports employees engaged in the recruitment of trial participants and is easy to integrate in their daily work.

**Supplementary Information:**

The online version contains supplementary material available at 10.1186/s13063-024-07918-z.

## Background

Clinical trials are the most important method for gaining new insights into the connection between medical treatments, environmental influences, and other factors on people’s health. Furthermore, only randomized controlled trials (RCTs) can provide conclusive evidence for causal effectiveness of new drugs and medical procedures on health. As the main link in the chain of evidence, RCTs are crucial for translating scientific results from basic research to clinical application [1, 2].

The success of clinical trials depends on the enrollment of a sufficiently large patient population. Failure to do so will result in reduced statistical power, ineffective use of human resources, and costly extensions to the trial duration [3, 4]. However, achieving the planned recruitment numbers remains one of the biggest challenges when conducting clinical trials [5–7]. As a consequence, sites in many countries have diminishing opportunities to participate in international studies and contribute to scientific progress. Further, many patients lose the chance to benefit from novel therapies that might have positive effects on their prognosis and quality of life [6, 8].

As an alternative to manual identification of eligible persons, technical solutions using data from electronic health records (EHR) have been developed to improve the inclusion of patients in clinical trials [9–11]. Initially aimed at supporting trial planning, those IT solutions informed how many patients with defined characteristics are available at a trial site (feasibility) [12]. Recently, there have been many approaches that help screening for eligible patients in the hospital information system (HIS) and directly suggest their inclusion into running trials [10, 11, 13, 14]. For some of these solutions, improvements in participant recruitment have been shown [15]. However, existing solutions often had either severe technical or methodological limitations or were not evaluated across multiple clinical sites.

The goal of the MIRACUM project [16], which is part of the German Medical Informatics Initiative [17], is to establish data integration centers across ten German university hospitals. The data integration centers shall transform the large and heterogenous amount of patient data into harmonized research repositories at each site. To demonstrate their effectiveness, three use cases in different clinical and application contexts were defined. Use Case 1 (UC1, Alerting in Care - IT Support for Patient Recruitment), aims to support the recruitment into clinical trials by automatically querying the repositories for patients satisfying the eligibility criteria and presenting them as screening candidates. To accomplish this, we developed software which leverages the OMOP Common Data Model (CDM) [18] and HL7 FHIR to provide an interoperable and open technical infrastructure for supporting the patient recruitment process [19].

The objective of this study is to investigate whether the developed recruitment tool has a positive effect on trial recruitment within a multi-center environment by increasing the number of participants. The secondary objective is the measurement of organizational burden and user satisfaction of the provided IT solution.

In the following, the presented evaluation is denominated as “study” and the clinical studies forming our target population as “trials”.

### Objectives

#### Hypotheses

The application of an IT-supported recruitment solution developed in the MIRACUM Use Case 1 (UC1) leads to an increased number of recruited participants in studies at German university hospitals. It supports employees engaged in recruitment of trial participants and is easy to integrate in their daily work.

#### Primary objective

To investigate whether the application of an IT-supported recruitment solution developed within the MIRACUM consortium is effective in increasing the number of recruited trial participants in studies at German university hospitals.

#### Secondary objective

To survey the subjective experience of the recruitment staff with the solution on (a) usability, (b) user satisfaction, and (c) efficacy, i.e., the support of the recruitment and inclusion processes.

## Methods

This study protocol has been developed adhering to the SPIRIT 2013 statement: Defining standard protocol items for clinical trials [20]. The completed SPIRIT 2013 Checklist is available as Supplementary File 1.

### Study design

The study uses an Interrupted Time Series (ITS) Design [21, 22] with a duration of 15 months. All trials start in the control phase of randomized length with regular recruitment and change to the intervention phase with additional IT support, ensuring a minimum of one month in each phase and a minimum trial observation of 6 months. At least one month prior to the inclusion of *a* specific trial into the study, the length of the control phase for this trial is randomized centrally across all 10 sites. A block randomization was used to randomize the time of switching to the new scheme in the percentage of the planned enrollment time into the study. We used R version 4.1.2 and the package blockrand version 1.5 with the seed 9384902. We allowed for values between 0.15 and 0.85 with 0.05 steps, rounding the resulting time of switching to the first or 15th of a month. We generated 5 blocks with a size of 30 resulting in 150 ids. When a study was enrolled at one of the sites, the site contacted the independent person at Freiburg, who took the next free id from the randomization list and relayed the time of switching for the specific study. The persons responsible for enrollment had no access to the randomization list.

Due to the embedding of the intervention into and its overlap with the recruitment processes, it is practically not feasible to completely blind the study. Nevertheless, the randomized time point to switch to the intervention will only be disclosed to the sites 2 months before and only subsequently to the medical staff. The effectiveness will be measured by the number of recruited participants per trial and week standardized by the targeted number of participants to be recruited into the specific trial. This will be analyzed by means of a linear mixed model. In addition, user interviews will be conducted prior to the start of the intervention and at the end of the study. 

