#### Time schedule

*Recruitment*: Trials are included starting on June 1, 2021.

*Randomization*: At least one month prior to the inclusion of *a specific* trial into the study, the length of the control phase for this trial is randomized centrally across all 10 sites.

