### Blinding

Due to the embedding of the intervention into and its overlap with the recruitment processes, it is practically not possible to completely blind the study. Nevertheless, the randomized time point to switch to the intervention will only be disclosed to the site’s medical staff 1 month before. The randomization list is generated prior to the start of the evaluation study by an independent statistician and kept secret.

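### The Study design section contradicts itself on when a site learns its switch date: at enrollment, or only 2 months before the switch

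*Protocol article*

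**What the plan says.** Four statements in the protocol article bear on who learns the switch date and when.

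- **Relay (Study design, first paragraph).** Enrollment of a trial prompts a call from the site to an independent person, described as the one "who took the next free id from the randomization list and relayed the time of switching for the specific study". As a safeguard, the article then adds: "The persons responsible for enrollment had no access to the randomization list".
- **Delayed disclosure to sites (Study design, second paragraph).** Full blinding is said not to be feasible. As mitigation, the switch point "will only be disclosed to the sites 2 months before and only subsequently to the medical staff".
- **Delayed disclosure to staff (Blinding).** The site's staff are told later still: "medical staff 1 month before". The list itself is generated in advance "by an independent statistician and kept secret".
- **Time of randomization (Study design and Time schedule).** At least one month before a trial enters the study, "the length of the control phase for this trial is randomized centrally across all 10 sites".

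The article does not say how enrollment of a trial, which triggers the contact, relates in time to its inclusion, which anchors the randomization and the start of the control phase.

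**The concern.** The site and the switch date are the same in the relay sentence and in the delayed-disclosure sentence. Only the timing differs, and for most allocations both cannot be true.

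The timing matters because delayed disclosure is what the plan offers in place of blinding. Under Intervention, local recruitment staff decide whether a proposed patient is included. The primary outcome is the weekly number recruited relative to expectation. People who know that the tool arrives on a given date can, knowingly or not, leave candidates until then. That lowers the control weeks and raises the intervention weeks, which favours the tool. The longer the date is known, the longer the window in which this can happen.

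A second route opens if the date is known before a trial's inclusion is final. The switch date is calculated from the inclusion date (Generation and implementation of allocation), so a site could re-time or withdraw a trial after seeing its allocation. Statistical methods excludes trials with deviations or missing data from the primary analysis, so a trial lost in this way might not be kept as allocated.

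**Working it through.** **Inputs.**
- Switch fractions: "We allowed for values between 0.15 and 0.85 with 0.05 steps" (Study design), that is 0.15, 0.20, …, 0.85, or (0.85 − 0.15)/0.05 + 1 = 15 values.
- Observation period per trial: 6 to 15 months (Generation and implementation of allocation).
- Notice to sites: 2 months (Study design). Notice to medical staff: 1 month (Blinding).
- Assumption: observation starts at enrollment, so that under the relay sentence the lead time equals the control phase.

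**The plan's own figures.** The article gives no lead time but does give minimum phase lengths. 0.15 × 6 = 0.9 months, stated as at least one month. 0.15 × 15 = 2.25 months, stated as 2.5. Neither difference changes the counts below: 0.9 and 1 are both under 2, and 2.25 and 2.5 are both over 2.

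**Comparison.** Control phase = fraction × observation period, before rounding of dates. The two rules conflict if the control phase exceeds 2 months. If it is shorter than 2 months, the 2-month notice falls before observation starts.

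| Observation period (months) | Fraction at which the control phase is 2 months | Control phase = lead time under relay (months) | Rules conflict | Notice precedes observation |
|---|---|---|---|---|
| 6 | 2/6 = 0.333 | 0.9 to 5.1 | 11/15 | 4/15 |
| 9 | 2/9 = 0.222 | 1.35 to 7.65 | 13/15 | 2/15 |
| 12 | 2/12 = 0.167 | 1.8 to 10.2 | 14/15 | 1/15 |
| 15 | 2/15 = 0.133 | 2.25 to 12.75 | 15/15 | 0/15 |

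At 6 months, for example, fractions 0.15, 0.20, 0.25 and 0.30 give 0.9, 1.2, 1.5 and 1.8 months. The next fraction, 0.35, gives 2.1. In a 15-month trial at the middle fraction, the site would know the date 0.50 × 15 = 7.5 months ahead, not 2.

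**How firm the counts are.**
- Rounding switch dates to the 1st or 15th moves a date by about a quarter of a month if it goes to the nearer one. Cases close to 2 months, such as 1.8 or 2.1, can then cross the line, so a count may change by about one fraction. The pattern does not.
- If the relay happened at the randomization, one month before inclusion, lead times would be one month longer. The rules would then conflict whenever the control phase exceeds 1 month: 14/15 at 6 months (all but 0.9) and 15/15 from 9 months on. The assumption used in the table is the milder one.

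**The case against.** **The list is protected.** Enrolling persons could not see it and it was kept secret. That stands, and it protects future allocations. It does not protect a date already relayed for the trial in question.

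**The relay sentence carries no separate date.** It could mean that the id was taken at enrollment and the date passed on later. The text does not separate the two acts, so the reader cannot tell. If that is what was meant, the repair is the same.

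**Other safeguards exist.** Switch times are randomized centrally, the mixed model adjusts for trial, site, season and time, and every trial receives both phases, so there is no untreated arm to avoid. This limits the concern but does not remove shifting of recruitment around a known date.

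**A journal article condenses.** Step-by-step release may well sit in the full protocol. But the article states two rules, and they disagree.

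Three stronger readings are tempting and not supported.
- *The 1-month and 2-month notices contradict each other.* They do not. One is for medical staff, the other for sites, and Study design says that staff are told after the site.
- *Sites know the allocation before inclusion as a rule.* The article does not say this. It times the randomization before inclusion and the relay at enrollment, without linking the two terms. Early knowledge follows only if the relay takes place at that earlier randomization, or where the control phase is shorter than the notice.
- *The bias can be put as a rate ratio.* Assuming that 20% of one month's recruits are deferred past the switch gives (1 + 0.2/5)/(1 − 0.2/5) = 1.08 for a 10-month trial switching midway, and (1 + 0.2/4.2)/(1 − 0.2/1.8) = 1.18 for a 6-month trial with a 1.8-month control phase. The 20% has no source in the article, and one month's deferral is equally possible under the planned 1-month notice. These ratios describe incomplete blinding, which the article admits, and not the contradiction.

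**Conclusion.** The contradiction within Study design stands. If observation starts at enrollment, it affects 11 of 15 allowed fractions in a 6-month trial, rising to all 15 in a 15-month trial, with a lead time there of 2.25 to 12.75 months against the stated 2. Taken as written, the relay sentence defeats the mitigation that the plan offers for incomplete blinding.

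A smaller, separate gap is that the 2-month notice cannot work as intended for control phases under 2 months: 4, 2, 1 and 0 of 15 fractions at 6, 9, 12 and 15 months, before rounding. In those cases the date could be known before inclusion even with the relay sentence removed.

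The size of any resulting bias cannot be derived from the article. Some shifting of recruitment is possible under any advance notice, and early relay lengthens the window. The point merits a correction because the repair is cheap and protects the main comparison. It does not by itself invalidate the design.

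**What to change.** 1. Reword the relay sentence in Study design. The independent person first logs the trial as irrevocably included, then draws the id and holds the date. The date is released no earlier than the notice already stated (2 months to the site, 1 month to its medical staff) and never before inclusion is logged. State how enrollment and inclusion relate.
2. Record for each trial the date on which the site, and then its staff, were actually told. The article describes allocation in the past tense. If it is complete, report what was done and recover these dates from the independent person's records.
3. Add a sensitivity analysis of the primary model that omits control weeks after disclosure, restricted to trials with control weeks remaining.

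**Cost.** The change needs some wording, one date field per recipient and one extra analysis. That analysis loses control weeks. With disclosure to the site 2 months ahead, a 6-month trial keeps 2.1 − 2 = 0.1 to 5.1 − 2 = 3.1 control months at fractions 0.35 to 0.85 and none at the four shortest, while a 15-month trial keeps 2.25 − 2 = 0.25 to 12.75 − 2 = 10.75. Sites with short control phases get less lead time for training and for the interviews planned before the intervention starts.

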### Settings

The study will be conducted at all university hospitals of the MIRACUM consortium partners within the BMBF Medical Informatics Initiative in the years 2021/2022 (Fig. 1):Dresden University of TechnologyFriedrich-Alexander University of Erlangen-NurembergUniversity Hospital FrankfurtAlbert Ludwig University FreiburgJustus Liebig University GiessenUniversity Medicine GreifswaldOtto-von-Guericke University MagdeburgJohannes Gutenberg University of MainzMedical Faculty Mannheim of the Ruprechts-Karls-University HeidelbergUniversity Hospital Gießen and Marburg

**Fig. 1 Fig1:**
[figure not shown]
Location of the participating university hospitals across Germany

### Participants

#### Eligibility criteria

Trials fulfilling the following criteria are included into the study:The specified inclusion and exclusion criteria can be formalized in a machine-processable wayThe recruitment phase of the trial is overlapping at least 6 months with the observation period of the study. Recruitment of patients into the trial is expected during the observation period.An individual trial can take part at one site or multiple sites. Usually, it takes part only at one site and is then included in the study as a single trial at the corresponding site; if *n* sites participate in a trial the trial is included *n* times at the corresponding sites.Prospective evaluation

Trials meeting the following criteria are excluded:Animal experimental studiesBiomaterial studiesTrials recruiting patients with psychiatric diagnosesPilot or feasibility trials

### Intervention

The intervention consists of the application of a complex recruitment-support system, which should be utilized alongside the standard recruitment procedure. Patient data, which is already collected in the context of general care, will be used for screening according to trial-specific criteria. The de-identified patient data, located in the data integration centers of the sites, are continuously compared against inclusion and exclusion criteria of clinical trials. This requires first translating the necessary eligibility criteria of all selected trials into a machine-readable format. The recruitment support system uses the OMOP common data model [18] to store patient data which includes OHDSI ATLAS as a tool for defining patient cohorts. ATLAS is a user interface where researchers can graphically define a cohort using a set of logical expressions that are internally converted to SQL to be executed against the database. This tool is used to identify and translate the eligibility criteria collaboratively with the trial personnel [23, 24]. During the intervention phase, all patient data is regularly checked against the defined cohorts. When eligible patients are detected, the staff is informed about the proposals by email, and the de-identified data is presented on a web-based screening list. The dataflow is shown in Fig. 2.

**Fig. 2 Fig2:**
[figure not shown]
The basic flow of data from the electronic health records (EHRs) to the research repositories to the creation of patient recommendations in the screening list. Treatment data is recorded in the EHR as part of routine care (1), this data is regularly transformed to the OMOP CDM via ETL jobs (2). A query module (3) continuously scans the research repository for patients matching the defined trial eligibility criteria. If potential candidates are found, they are put on a web-based screening list (4), and a notification is sent via email. This notification is received by relevant practitioners or trial personnel (5) and the screening list can be accessed to further manually screen the suggested patients

Local recruitment staff decides over inclusion of individual patients based on the recruitment proposals on the screening list. Patient status, from recruitment proposal to inclusion, is documented in the screening list. Because it is based on pseudonymized research data, by default, this list displays only a pseudonymized medical record number, the year of birth, the gender, and the last known organizational unit within the hospital. This data can be used to either search the hospital information system with its applicable access controls, or the study personnel has to contact the attending physician based on the last known location of the patient. After consenting to disclose trial and personal data, the staff can then inform the patient about a possible participation in the trial. Some sites allow displaying the re-identified medical record number to make it easier to identify the patient. In these cases, re-identification works by technically integrating the screening list with the pseudonymization tooling established at the sites.

In the control phase, trial participants are recruited according to the respective standard procedure.

Termination criteria are not defined, since the interventional IT solution is used parallel to the conventional solution.

To increase the adherence of the recruiting staff, training courses are conducted and regular visits take place. Problems with adherence are logged.

